Optimized heart failure therapy for at least 1 month prior to enrolment	Terminal illness with limited life expectancy (e.g., metastatic cancer, end-stage lung disease)
Any LVEF phenotype (HFrEF, HFmrEF, HFpEF)	Pregnancy
≥1 hospitalization or outpatient visit with IV therapy for CHF in last 12 months	Dermatological conditions or allergies preventing prolonged use of the wearable device
Ability to provide informed consent or availability of a legally authorized representative	Cognitive or psychiatric disorders impairing adherence to study procedures

CHF, chronic heart failure; eGFR, estimated Glomerular Filtration Rate; HFmrEF, Heart Failure with mildly reduced Ejection Fraction; HFpEF: Heart Failure with preserved Ejection Fraction; HFrEF, Heart Failure with reduced Ejection Fraction; IV, intravenous; LVEF, left ventricular ejection fraction; NYHA, New York Heart Association; VAD, ventricular assist device.

All clinical, instrumental, and biochemical data will be recorded in anonymized case report forms and stored in a secure digital database. Biospecimens (blood and urine) will be collected and retained for secondary biomarker analysis. The study protocol adheres to the Declaration of Helsinki and Good Clinical Practice guidelines, and it was approved by the regional ethics committee (Comitato Etico Campania 2; Approval No. 185867). The trial is registered at ClinicalTrials.gov with the identifier NCT06909682.

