### Outcomes

2.4

Both groups will undergo assessments at baseline, 3 months, and 6 months, including evaluations of functional status, echocardiographic parameters, biochemical markers (e.g., BNP, NT-proBNP, renal function), and quality of life assessed using the Kansas City Cardiomyopathy Questionnaire (KCCQ) (36–39) (Table 2).

**Table 2 T2:** SMART-CARE outcome measures by timepoint.

Outcome type	Outcome measure	Domain	Baseline	3 months	6 months
Primary	Change in Hospital Admissions	Clinical Events			✔
Secondary	Change in Quality of Life (KCCQ Score)	Quality of Life	✔	✔	✔
Secondary	Adverse Effects of CHF Therapy	Safety			✔
Secondary	Change in BNP Levels	Biochemical	✔	✔	✔
Secondary	Change in NT-proBNP Levels	Biochemical	✔	✔	✔
Secondary	Change in Serum Creatinine	Biochemical	✔	✔	✔
Secondary	Change in eGFR	Biochemical	✔	✔	✔
Secondary	Change in Serum Sodium	Biochemical	✔	✔	✔
Secondary	Change in Serum Potassium	Biochemical	✔	✔	✔
Secondary	Change in Serum Chloride	Biochemical	✔	✔	✔
Secondary	Change in HRV	Functional (ECG)	✔	✔	✔
Secondary	Change in Respiratory Rate	Functional (ECG)	✔	✔	✔
Secondary	Change in LVEF	Echocardiographic	✔	✔	✔
Secondary	Change in E/A Ratio	Echocardiographic	✔	✔	✔
Secondary	Change in LV End-Diastolic Volume	Echocardiographic	✔	✔	✔
Secondary	Change in LV End-Systolic Volume	Echocardiographic	✔	✔	✔

CHF, chronic heart failure; KCCQ, Kansas City Cardiomyopathy Questionnaire; BNP, B-type Natriuretic Peptide; NT-proBNP, N-terminal pro-B-type Natriuretic Peptide; eGFR, estimated Glomerular Filtration Rate; HRV, Heart Rate Variability; ECG, Electrocardiogram; LVEF, Left Ventricular Ejection Fraction; E/A Ratio, Early to Late Ventricular Filling Velocity Ratio; LV, left ventricle.

The primary outcome of the SMART-CARE study is the relative reduction (≥20%) in hospital admissions, including emergency department visits and unplanned hospitalizations, over a six-month follow-up period in the intervention group compared to standard care (40). Hospitalization data will be collected prospectively and analysed for frequency, duration, and cause.

Secondary outcomes include:

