#### Primary endpoint analysis

2.6.1

To assess the primary endpoint of the study, Kaplan–Meier survival curves will be constructed to compare the time to first hospitalization between groups. Group differences will be evaluated using the log-rank test. Subsequently, a Cox proportional hazards regression analysis model will be performed to examine the association between the variable “Device Use (Yes vs. No)” and the reduction in hospital admissions. The model will be adjusted for all statistically significant covariates identified through ANOVA between the two groups. To mitigate selection bias resulting from the non-randomized design, propensity score methods will be applied. The propensity score will be estimated using baseline variables including age, sex, LVEF phenotype, NYHA class, major comorbidities (hypertension, atrial fibrillation, diabetes mellitus, COPD/OSA, obesity), prior HF hospitalizations, baseline biomarkers (BNP/NT-proBNP, renal function, electrolytes), and key echocardiographic indices (LVEF, LV volumes). A 1:1 nearest-neighbour matching approach without replacement will be used. Covariate balance between groups will be evaluated using standardized mean differences (SMD), with values <0.10 indicating adequate balance. Results will be expressed as hazard ratios (HR) with corresponding 95% confidence intervals (CI).

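### The primary outcome is not limited to heart failure, but the only prior hospital use named in the propensity score is; prior emergency visits and non-HF admissions should be named and checked for balance

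*Protocol article*

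**What the plan says.** **Outcome.** Section 2.4 defines the primary outcome as a relative reduction of at least 20% in "hospital admissions, including emergency department visits and unplanned hospitalizations, over a six-month follow-up period in the intervention group compared to standard care". It adds that "Hospitalization data will be collected prospectively and analysed for frequency, duration, and cause". Section 2.6.3 sizes the study on the same combination of ED visits and hospitalizations. Neither section limits the events to heart failure. The term all-cause is not used, but recording cause as something to be analysed fits a count that includes other causes.

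**Groups.** Sections 2.1 and 2.2 form the groups by the patient's acceptance of the device, without randomization.

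**Adjustment.** In section 2.6.1, "The propensity score will be estimated using baseline variables including age, sex, LVEF phenotype, NYHA class", followed by "major comorbidities (hypertension, atrial fibrillation, diabetes mellitus, COPD/OSA, obesity), prior HF hospitalizations, baseline biomarkers (BNP/NT-proBNP, renal function, electrolytes", and echocardiographic indices. Matching is 1:1 nearest neighbour, with SMD below 0.10 as the mark of adequate balance. The Cox model is also adjusted for covariates that differ significantly between groups; the candidates are not listed.

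**Entry rule.** Table 1 requires "≥1 hospitalization or outpatient visit with IV therapy for CHF in last 12 months", which is also specific to heart failure.

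**Table 2.** The primary row is labelled "Change in Hospital Admissions" and is ticked at 6 months only.

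**The concern.** In a self-selected comparison, the covariates in the propensity score carry much of the weight of the primary result. A patient's past count of the outcome's own events is the most direct measured proxy for care-seeking, frailty and non-cardiac illness. Willingness to wear a monitor for six months could plausibly go with all three. The plan names the HF part of that history and leaves the rest unnamed, although the rest also counts as outcome events. If acceptors habitually use the ED less or have fewer non-HF admissions, some of that difference would be credited to the device. The SMD rule gives no warning, because it is applied to the covariates that are entered.

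**Working it through.** The plan states no figure on this point, so there is none to reproduce. The check has two parts.

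**1. Events counted against history named**

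| Event type | Counted in the outcome (2.4, 2.6.3) | Prior history named in the propensity score (2.6.1) |
|---|---|---|
| HF hospitalization | yes | yes |
| Unplanned non-HF hospitalization | yes, as no cause is excluded | no |
| ED visit | yes | no |

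**2. How large a bias could be**

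None of the inputs below is in the documents; all are assumptions. Suppose there is no device effect. A share p_C of controls and p_D of device users have a history of ED or non-HF use, and that history multiplies the event rate by R. The apparent rate ratio is then

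(1 + p_D(R − 1)) / (1 + p_C(R − 1)),

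and the imbalance is

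SMD = (p_C − p_D) / √{[p_C(1 − p_C) + p_D(1 − p_D)] / 2}.

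Worked example with p_C = 0.40, p_D = 0.30, R = 2: 1.30 / 1.40 = 0.93, and SMD = 0.10 / √[(0.24 + 0.21) / 2] = 0.21.

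| p_C, p_D | SMD | R = 1.5 | R = 2 | R = 2.5 | R = 3 |
|---|---|---|---|---|---|
| 0.40, 0.35 | 0.10 | 0.98 | 0.96 | 0.95 | 0.94 |
| 0.40, 0.30 | 0.21 | 0.96 | 0.93 | 0.91 | 0.89 |
| 0.40, 0.20 | 0.45 | 0.92 | 0.86 | 0.81 | 0.78 |

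These are apparent reductions of about 2 to 6%, 4 to 11% and 8 to 22%. The imbalance should be read as what remains after matching on the named covariates. The first row sits at about the plan's own balance limit, so holding this history to that limit would confine the bias to roughly the first row.

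**How much the extra covariate helps.** A Poisson simulation with no device effect used these assumptions:
- 300 patients with at least one HF event in the past year, and an HF event rate of 0.8 per year;
- other admissions and ED visits making up 40 to 60% of all events;
- log-frailty SD 0.7;
- acceptors 0.30 to 0.47 SD healthier on non-HF frailty;
- a comorbidity proxy correlated 0.5 with that frailty.

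Adjusting for the prior HF count and the proxy left a spurious rate ratio of 0.85 to 0.94. Adding the prior count of other admissions and ED visits moved it to 0.89 to 0.96. On the log scale, pairing the ends of the ranges, the share of bias removed is 1 − ln 0.89 / ln 0.85 = 28% and 1 − ln 0.96 / ln 0.94 = 34%, or about a third.

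**The case against.** The strongest reply is that the covariate list is open: it is introduced as baseline variables including those named, and a journal article may leave the complete list to the full protocol. Prior HF hospitalizations are themselves part of the counted events. The comorbidities, biomarkers and NYHA class stand in partly for non-HF use, the Cox model may add covariates that differ between groups, and section 5 already acknowledges selection bias. All of this is fair, and it limits the point to what is named and checked. It does not remove the mismatch. The list is detailed enough to include electrolytes and ventricular volumes, and it specifies a utilisation history narrower than the outcome. The Cox route can pick up only a variable that has been collected.

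The simulation also has limits. It uses Poisson counts and a single proxy, not the planned matched time-to-first-event analysis with its longer covariate list.

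Three stronger inferences are tempting and do not hold:

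- **That the prior HF variable hardly varies because entry requires a recent HF event.** Table 1 also admits patients through an outpatient visit with IV therapy, so prior HF hospitalizations can be zero, and section 2.6.1 sets no 12-month window for the covariate.
- **That the blank baseline cell in Table 2 shows prior admissions are not collected.** Table 2 lists outcomes by timepoint, not covariates, and the adverse-effects row is likewise ticked only at month 6.
- **That the primary result could be a before-after change, open to regression to the mean.** Sections 2.4, 2.6.1 and 2.6.3 all define a between-group comparison, and both groups meet the same entry rule. Only a loose row label remains.

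**Conclusion.** The point holds as a mismatch between the breadth of the outcome and the breadth of the named adjustment. Prior ED visits and non-HF admissions are not named for the propensity score, so their balance between self-selected groups is neither assured nor covered by the SMD check. A reader might go further and conclude that the groups will in fact be unbalanced on this history. The text does not support that, because the list is open and other covariates give partial control.

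The possible bias runs from a few percent to about 20%, against a 20% target, depending entirely on the assumed imbalance and on how strongly past use predicts future use. Naming the covariate is a modest improvement: in the simulation it removed about a third of the residual bias. It is worth making because it is cheap and the primary comparison relies on this adjustment.

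**What to change.** 1. Record at baseline each patient's unplanned admissions of any cause and ED visits in the 12 months before enrolment, from the same source and with the same definition as at follow-up.
2. In section 2.6.1, name this count in the propensity score and in the adjusted Cox model, next to prior HF hospitalizations, and report its SMD against the 0.10 limit.
3. As a minor wording point, relabel the Table 2 row "Change in Hospital Admissions" as admissions and ED visits over six months, device versus control, to match section 2.4.

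The cost is one retrospective item per patient and a line each in section 2.6.1 and Table 2. The drawback is that visits to other hospitals may be under-recorded, so the count will be an imperfect measure of past use.

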#### Secondary endpoint analysis

2.6.2

Continuous variables will be presented as mean ± standard deviation (SD) for normally distributed data and as median and interquartile range (IQR) for non-normally distributed data. Categorical variables will be expressed as frequencies and percentages. The normality of distribution will be tested using the Shapiro–Wilk test. For normally distributed continuous variables, comparisons will be made using the paired t-test or one-way repeated measures ANOVA, depending on the situation. For non-normally distributed data, the Wilcoxon Signed-Rank test will be applied. Categorical variables will be compared using the Pearson chi-square test. Given the intrinsic differences in echocardiographic and clinical trajectories between HFrEF and HFpEF patients, all secondary endpoints (including echocardiographic parameters, biomarkers, and functional indices) will also undergo stratified analyses by LVEF phenotype. This approach is intended to avoid the dilution of clinically meaningful changes in subgroups with limited baseline variability, particularly among HFpEF patients. Subgroup analyses based on LVEF phenotype (HFrEF, HFmrEF, HFpEF) will be performed as exploratory analyses. The study is not powered to detect statistically significant differences between these subgroups; therefore, these analyses are intended to be descriptive and hypothesis-generating. To mitigate potential confounding when comparing phenotypes, LVEF category will be included as a covariate in multivariable models, and propensity score techniques will be applied when appropriate. Because echocardiographic parameters show markedly different baseline ranges and variability in HFrEF and HFpEF, echocardiographic secondary outcomes will also be interpreted within each LVEF phenotype. This approach is intended to avoid the dilution of true within-group changes in HFpEF patients, in whom structural parameters often fall within or near the normal range. A two-sided *p*-value < 0.05 will be considered statistically significant for all final analyses.

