**Results:**

We hypothesize that AI-driven remote monitoring will significantly reduce hospitalizations, improve quality of life, and favorably impact biochemical and echocardiographic parameters compared to standard care.

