### Groups and interventions

2.2

Participants will be allocated to one of two non-randomized, parallel groups based on their acceptance to use the wearable device:
Intervention Group – AI-Based Remote Monitoring: Patients in this group will wear wearable devices continuously over a six-month period. The wearable device collects multimodal biometric data, including SpO₂, HRV, EDA, respiratory rate, skin temperature, pulse rate, and sleep metrics (actigraphy). These data are automatically transmitted to the SMART-CARE platform, where advanced AI algorithms analyse trends and detect early signs of clinical deterioration. In case of abnormal findings, the system generates alerts for the clinical team, which may initiate teleconsultations, therapy adjustments, or in-person evaluations to prevent acute decompensation.Control Group – Standard Clinical Follow-Up: Participants in the control group will receive standard CHF management in accordance with current European Society of Cardiology (ESC) guidelines. This includes outpatient visits every three months, ECG and echocardiographic assessments, and laboratory evaluations. No remote monitoring will be applied in this group. Clinical decisions, including medication adjustments, will be based on periodic clinical evaluations and patient-reported symptoms.

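### For quality of life, biomarkers and echocardiography the plan names only within-patient tests, so the hypothesis of benefit over standard care has no stated device-versus-control test

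*Protocol article*

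**What the plan says.** The abstract expects AI-driven monitoring to "improve quality of life, and favorably impact biochemical and echocardiographic parameters compared to standard care". Section 2.2 sets up the comparison: "Participants will be allocated to one of two non-randomized, parallel groups based on their acceptance to use the wearable device". Section 2.4 schedules the same visits for everyone: "Both groups will undergo assessments at baseline, 3 months, and 6 months".

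Section 2.6.2 then fixes the tests:
- Normally distributed continuous variables: "comparisons will be made using the paired t-test or one-way repeated measures ANOVA, depending on the situation".
- Other continuous variables: "For non-normally distributed data, the Wilcoxon Signed-Rank test will be applied".
- Categorical variables: "Categorical variables will be compared using the Pearson chi-square test".

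Multivariable modelling enters section 2.6.2 for a different purpose: "To mitigate potential confounding when comparing phenotypes, LVEF category will be included as a covariate in multivariable models". The only analyses that explicitly set device against control are the log-rank test and the Cox model with a device-use term in section 2.6.1, and both serve the primary endpoint.

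**The concern.** The hypothesis is a contrast between two groups, but the tests named for it look at one group at a time. A paired t-test and a signed-rank test ask whether a patient's later value differs from the earlier one. A one-way repeated measures ANOVA has visit as its factor and no group term.

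Both groups could change over six months without any device effect. Table 1 requires a hospitalisation or an outpatient visit with IV therapy for CHF in the previous 12 months, and controls receive guideline care with three-monthly visits. A significant change in the device group would then say nothing about benefit over standard care. A significant change in one group but not in the other is easily misread as a difference between them. Because patients choose their group, within-group p-values are weaker evidence still.

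**Working it through.** **Step 1: match the hypothesis to the tests.** Table 2 lists 15 secondary outcomes.

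| Domain | Outcomes | In the abstract's hypothesis | Test named in 2.6.2 |
|---|---|---|---|
| Quality of life (KCCQ) | 1 | yes | within-patient |
| Biochemical | 7 | yes | within-patient |
| Echocardiographic | 4 | yes | within-patient |
| HRV, respiratory rate | 2 | not named | within-patient |
| Adverse effects | 1 | not named | chi-square, which can compare groups |

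The hypothesis covers 1 + 7 + 4 = 12 of the 15. For these 12, section 2.6.2 names no unpaired t-test, rank-sum test, ANCOVA, group-by-visit term or mixed model.

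**Step 2: how often a within-device test is significant when the device does nothing.** The plan gives no figure to reproduce here. Inputs:
- Two-sided alpha 0.05 (section 2.6.2).
- Enrolment 300 and 10% dropout (section 2.6.3). Assuming equal groups, n = 300 × 0.90 / 2 = 135 per group. The article states no allocation ratio.
- A common true change of d standard deviations of change in both groups. The article gives no value, so a range is shown.

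The noncentrality of the paired t-test is d × √n, with 134 degrees of freedom and critical value 1.978. At d = 0.25 (for example 5 KCCQ points with an SD of change of 20, both assumed) it is 0.25 × √135 = 2.90, which gives p = 0.822. With independent groups, the chance that the device group is significant and the control group is not is p(1 − p) = 0.822 × 0.178 = 0.146.

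| d | device group significant, p | device significant, control not, p(1 − p) |
|---|---|---|
| 0.10 | 21% | 17% |
| 0.15 | 41% | 24% |
| 0.20 | 64% | 23% |
| 0.25 | 82% | 15% |
| 0.30 | 93% | 6% |

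**Step 3: sensitivity to group size.** With 150 per group and a normal approximation, the device group is significant 23% of the time at d = 0.10, 69% at 0.20 and 96% at 0.30. With an assumed 200:100 split in favour of the device, the device group is significant and the control group is not about 39% of the time at d = 0.20. With the reverse split it is about 10%.

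**Step 4: the comparator.** A between-group test of change rejects 5% of the time when both groups change equally, provided that confounding has been dealt with.

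**The case against.** The strongest reply is that between-group methods do appear elsewhere. Section 2.1 promises multivariable regression, propensity score matching and stratified analyses for the study as a whole. Section 2.6.1 describes 1:1 matching, and on matched pairs a paired t-test or signed-rank test would be a device-versus-control test. Section 2.6.2 does not say what is paired. The text does not carry this reading:
- Matching is described only under the primary endpoint.
- The general promise in section 2.1 names no model for any secondary outcome.
- The propensity wording in section 2.6.2 concerns comparisons between LVEF phenotypes.
- One-way repeated measures ANOVA has no group factor.

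A separate analysis plan may add a between-group model. But the article names specific tests that do not address its hypothesis, which goes beyond leaving out detail.

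Parts of the reply do stand. Entry requires clinical stability and at least one month of optimised therapy, which may reduce a shared change over time without excluding it. The primary endpoint has explicit between-group tests and is untouched.

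A reader might also infer more than the documents support:
- That no secondary outcome can be compared between groups. The chi-square test can do this for adverse events.
- That all 14 secondary outcomes other than adverse effects belong to the untested hypothesis. HRV and respiratory rate are not named in it. Section 2.4 derives them from wearable data, and section 2.2 rules out remote monitoring in controls, so control values may not exist.
- That patients with a missed visit simply drop out of the repeated measures ANOVA. Section 2.6.4 plans multiple imputation when data are missing at random.
- That the error to fear at 0.25 SD is the 2 × 0.822 × 0.178 = 29% chance that exactly one group is significant. That counts both directions; the direction favouring the device is about 15%.

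**Conclusion.** The point holds for 12 of the 15 secondary outcomes. The abstract claims benefit over standard care in quality of life, biochemistry and echocardiography, and section 2.6.2 names only within-patient tests for them. Carrying out those tests as written would leave the claim untested.

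With no device effect, the within-device test would be significant about 21% to 93% of the time for shared changes of 0.10 to 0.30 SD, and 82% at 0.25 SD. The misleading pattern of device significant and control not would occur about 15% of the time at 0.25 SD. These figures assume 135 patients per group and an equal change in both. Neither the group sizes nor any SD is stated, so they illustrate the risk and do not predict it. The 5% for a between-group test holds only if adjustment for self-selection succeeds. The conclusion that the comparison is missing rests on the named tests and needs none of these assumptions.

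**What to change.** For each of the 12 outcomes, state one adjusted between-group analysis in section 2.6.2. Either ANCOVA of the 6-month value or a mixed model with group, visit, group-by-visit and baseline value would do. Use the propensity-matched set or the covariates that the plan already lists in section 2.6.1. Report the device-minus-control difference at 6 months with its 95% CI, and label within-group tests as descriptive.

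For HRV and respiratory rate, first reconcile three statements: section 2.4 takes them from wearable data, Table 2 lists them as ECG measures at all visits, and section 2.2 excludes remote monitoring in controls. Specify a between-group comparison only once it is clear that controls have comparable values.

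The cost for the 12 outcomes is a change of wording. Both groups are already assessed at baseline, 3 and 6 months, so no new data are needed. With an assumed 150 per group, the unadjusted detectable difference would be about 0.32 SD at 80% power, from (1.96 + 0.84) × √(2/150). Stating this would help readers judge what the secondary comparisons can show.

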### Study design and population

2.1

The SMART-CARE study is a multicenter, prospective, observational cohort trial, designed to evaluate the clinical utility of artificial intelligence (AI)-enabled remote monitoring in patients with CHF. A prospective, non-randomized observational design was chosen for both ethical and pragmatic reasons. Allocation to the intervention group required patients' explicit willingness to use the wearable device and to undergo continuous monitoring, making randomization unfeasible. To minimize potential selection bias, statistical adjustment methods (multivariable regression, propensity score matching, and stratified analyses by age, sex, New York Heart Association class - NYHA, Left Ventricular Ejection Fraction - LVEF phenotype, and comorbidities) will be applied. The trial will be conducted across three tertiary care centers in Italy: AOU “San Giovanni di Dio Ruggi d'Aragona”, IRCCS Neurolesi “Bonino Pulejo”, and IRCCS Fondazione Casa Sollievo della Sofferenza. The study will enroll 300 adult patients (≥18 years) with a confirmed diagnosis of CHF, including Heart Failure with reduced Ejection Fraction (HFrEF), Heart Failure with mildly reduced Ejection Fraction (HFmrEF), or Heart Failure with preserved Ejection Fraction (HFpEF) for at least six months, who are clinically stable and on optimized medical therapy for at least one month prior to enrolment (Figure 1).

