Quality of Life (QoL): Measured using KCCQ at baseline, 3 months, and 6 months.Biochemical parameters: BNP, NT-proBNP, serum creatinine, eGFR, and serum electrolyte levels (sodium, potassium, chloride) at 3 and 6 months.Functional parameters: Variations in HRV and RR derived from wearable sensor data.Echocardiographic measures: LVEF, Early to Late Ventricular Filling Velocity Ratio (E/A ratio), and left ventricular end-diastolic and end-systolic volumes, measured at 3 and 6 months.Adverse events: Incidence of therapy-related complications such as hypotension and bradyarrhythmias.These outcomes will provide a comprehensive evaluation of the impact of AI-driven remote monitoring clinical status, functional performance, biomarker trends, and patient-reported outcomes in individuals with CHF. The measurements collected by the minimally invasive devices will be uploaded to the “Smartcare” platform and analyzed using machine learning (ML) techniques to develop multiparametric scores capable of identifying the specific trajectory of patients affected by HF.

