## Expected results

3

We anticipate that AI-based remote monitoring with the integration of wearable devices will lead to a ≥20% reduction in hospital admissions over six months compared to standard care. Furthermore, we expect improvements in secondary outcomes, including enhanced quality of life, reduced therapy-related adverse events, and more favourable trends in biochemical and echocardiographic parameters. By enabling early detection of clinical deterioration and supporting timely intervention, the SMART-CARE system is expected to offer a more proactive, individualized, and data-driven approach to managing CHF. These findings may support the integration of wearable technologies and AI into routine clinical practice for heart failure patients, potentially reducing the burden on healthcare systems and improving long-term patient outcomes.

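### Section 2.6.2 names only an unadjusted chi-square for adverse-event incidence and does not carry through the study-wide promise to adjust for self-selection

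*Protocol article*

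**What the plan says.** **Group formation.** Section 2.2: "Participants will be allocated to one of two non-randomized, parallel groups based on their acceptance to use the wearable device".

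**Study-wide commitment.** Section 2.1: "To minimize potential selection bias, statistical adjustment methods (multivariable regression, propensity score matching, and stratified analyses by age, sex, New York Heart Association class", with the list going on to ejection-fraction phenotype and comorbidities. Nothing there restricts the commitment to the primary endpoint. Section 5 relies on it again when it discusses the non-randomized design.

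**Primary endpoint.** Section 2.6.1 puts the commitment into practice: "To mitigate selection bias resulting from the non-randomized design, propensity score methods will be applied". It lists the score variables, specifies 1:1 nearest-neighbour matching without replacement, and sets a balance threshold on standardized mean differences.

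**Secondary endpoints.** For categorical data, section 2.6.2 says "Categorical variables will be compared using the Pearson chi-square test". Its one sentence on adjustment reads "To mitigate potential confounding when comparing phenotypes, LVEF category will be included as a covariate in multivariable models" and then adds propensity techniques where judged suitable. Significance is two-sided 0.05 for all final analyses.

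**The safety outcome.** Section 2.4 defines it as "Incidence of therapy-related complications such as hypotension and bradyarrhythmias". Table 2 lists it as secondary and ticks it at 6 months only. Section 3 expects "reduced therapy-related adverse events".

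**The concern.** Section 2.1 treats self-selection as a threat that needs adjustment. Section 2.6.1 acts on this for hospital admissions. Section 2.6.2 names a specific test for categorical outcomes and attaches no adjustment for device versus control. An analyst who follows 2.6.2 as written would compare adverse-event proportions between acceptors and decliners with no correction for how the groups arose, and would judge the result at p < 0.05.

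At stake is a conclusion that the article already anticipates, namely fewer therapy-related adverse events with the device. Section 5 notes that older or less digitally literate patients may be under-represented in the device group. If acceptors carry a lower baseline risk of hypotension or bradyarrhythmia, a crude test can show a benefit with no device effect. If they carry a higher risk, or if closer surveillance leads to more events being recorded among them, a crude test can hide a benefit or suggest harm.

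**Working it through.** **1. Which test applies.** Table 2 has 15 secondary outcomes. Fourteen are changes in a measured quantity, and the fifteenth is adverse effects of therapy. The other tests in 2.6.2 (paired t-test, repeated-measures ANOVA, Wilcoxon signed-rank) do not fit an incidence, so the chi-square is the only named test that does. This link is inferred from the outcome type, because 2.6.2 does not tie the chi-square to adverse events by name.

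**2. Which adjustment applies.** The stated purpose of each passage differs:
- 2.1: selection bias, whole study, no endpoint named.
- 2.6.1: selection bias, primary endpoint, method given in detail.
- 2.6.2: confounding between phenotypes, with propensity techniques left conditional.

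No sentence in 2.6.2 gives an adjusted device-versus-control analysis of adverse events.

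**3. How far selection alone could move a crude comparison.** The article states no adverse-event rate, group split or power for this outcome, so there is no figure of its own to reproduce. All inputs here are assumptions, except the total of 300 and the two-sided alpha of 0.05 (section 2.6.3).

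Assume 150 per group and no device effect. Let a baseline risk factor (frailty, say) have prevalence f in a group and multiply the six-month event risk by k, with risk 10% when it is absent. The group risk is then 0.10 × [1 + (k − 1)f].

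The chance of a significant result favouring the device is approximately Φ[(p_c − p_d − 1.96·SE0)/SE1], where SE0 = √[2p̄(1 − p̄)/150] and SE1 = √{[p_c(1 − p_c) + p_d(1 − p_d)]/150}.

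| f, control vs device | k | Control risk | Device risk | Crude RR | Chance |
|---|---|---|---|---|---|
| 40% vs 40% | 2 | 14.0% | 14.0% | 1.00 | 2.5% |
| 40% vs 30% | 2 | 14.0% | 13.0% | 0.93 | 4.4% |
| 50% vs 30% | 3 | 20.0% | 16.0% | 0.80 | 14.5% |
| 50% vs 20% | 3 | 20.0% | 14.0% | 0.70 | 28.1% |

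Third row worked through: p̄ = 0.18, SE0 = √(2 × 0.18 × 0.82/150) = 0.0444, SE1 = √[(0.16 + 0.1344)/150] = 0.0443. Then (0.04 − 1.96 × 0.0444)/0.0443 ≈ −1.06, and Φ(−1.06) ≈ 0.145.

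Swapping the two prevalences gives the same chances of a false result against the device, so the direction is not fixed.

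**4. Follow-up time.** Planned follow-up is six months in both groups. Assume a constant hazard, a six-month risk of 15% or 30% in both groups, dropout spread evenly over the period, and dropouts without an event counted as event-free. With 6h = −ln(1 − p), the observed risk among dropouts is 1 − p/(6h).
- 10% dropout in both groups (the planning figure in 2.6.3): RR 1.00.
- 5% control vs 15% device: RR about 0.95, chance of false benefit 3.8% to 4.6%.
- 0% control vs 20% device: RR 0.90 to 0.91, chance 5.5% to 7.8%.

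Example for p = 15%: 6h = 0.1625, and the dropout risk is 1 − 0.15/0.1625 = 0.077. The device group has 0.85 × 0.15 + 0.15 × 0.077 = 0.139, and control has 0.95 × 0.15 + 0.05 × 0.077 = 0.146. The ratio is 0.95.

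**The case against.** The strongest reply is that section 2.1 already promises adjustment and matching for the study as a whole and section 5 repeats it. A chi-square could be run in the matched set, and a condensed article may leave the exact model to a fuller document. This stands in part. A reader might infer that the safety comparison is planned to be crude and nothing else, and the documents do not show that. They show a general promise that does not reach the section where the test is chosen, while the only adjustment sentence in that section serves another purpose.

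A reader might also infer that a patient who leaves or dies early is counted as event-free for six months. No passage says so. Section 2.6.4 covers incomplete follow-up with multiple imputation, complete-case and extreme-case sensitivity analyses, and per-protocol and intention-to-monitor analyses. Its censoring rule is confined to time-to-event analyses, so how unequal follow-up enters a comparison of proportions is not stated. As step 4 shows, the resulting bias is small and needs dropout to differ between groups.

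Larger figures can be produced by simply positing a risk gap. Exact enumeration at 150 per group gives two-sided rejection in 21% of trials at 15% vs 20%, and in 48% at 8% vs 15%. The arithmetic is right, but these gaps imply risk ratios of 0.75 and 0.53 with no confounder specified to produce them. The second goes beyond even the strongest scenario in step 3 (0.70), and the rates count rejections in both directions.

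Finally, section 5 says only that older or less digitally literate patients might be under-represented, and raises this as a matter of generalizability. It does not predict an imbalance of any given size.

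**Conclusion.** The point holds as an inconsistency between sections 2.1 and 2.6.2. The one test named for categorical secondary outcomes is unadjusted and by outcome type covers adverse-event incidence. The promised adjustment for self-selection is not applied there to device versus control. A crude difference could therefore reflect who accepted the device, in either direction.

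The size cannot be taken from the document. Under the scenarios above, the chance of a false benefit runs from just above nominal (4.4% vs 2.5%) to about eleven times nominal (28.1%). This rests on the assumed equal split, the 10% base risk, and the assumed prevalence and strength of the confounder. Follow-up time is a minor, conditional part of the point. The change should be made, but the text does not establish that the safety analysis will be unadjusted.

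**What to change.** State in section 2.6.2 that the device-versus-control comparison of adverse events uses the propensity score of section 2.6.1, either as a matched comparison or as a propensity-adjusted model for a binary outcome. Report an adjusted risk ratio or risk difference with 95% CI, and keep the crude chi-square as descriptive only.

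Where onset dates or time at risk are recorded, account for follow-up with a time-to-first-event model or a rate model with log follow-up as offset. Otherwise, say that the rules of section 2.6.4 apply to patients with incomplete follow-up.

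**Cost.** The score is already planned, so the adjusted binary comparison needs only a change of wording. The interval will be wider than the crude one, and reusing 1:1 matching discards unmatched patients. The time-based version may need more than wording: the primary analysis requires hospitalization dates, not onset dates of hypotension or bradyarrhythmia, and Table 2 ticks adverse effects at 6 months only. Adjustment removes only the imbalance that the score's variables capture. Frailty and digital literacy are not among them, and differences in surveillance between the groups would also remain, so the safety result should still be worded with caution.
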